## 2.5 SAE REPORTING FLOWCHART

[figure not shown]

## 2.6 SERIOUS BREACHES AND URGENT SAFETY MEASURES

If a possible protocol violation and/or GCP breach has been identified during the trial, the CI will assess if the event affects the safety, physical or mental integrity of the trial subject or the scientific value of the study. Any possible serious breaches should be investigated further and the event should be reported to the Sponsor immediately. Where a serious breach has occurred, the Sponsor will ensure that the MHRA have been notified within 7 days of becoming aware of that breach.

The Sponsor or investigator may take appropriate urgent safety measures in order to protect the patient of a clinical trial against any immediate hazard to their health or safety. This includes procedures to protect patients from pandemics or infections that pose serious risk to human health. Urgent safety measures may be taken without prior authorisation from the MHRA and REC. The Sponsor must notify the MHRA and REC immediately and in writing within three days of such measures being taken.

## 2.7 CONTRACEPTION AND PREGNANCY REPORTING

The Investigator must make every effort to try and ensure that a clinical trial patient or a partner of a clinical trial patient does not become pregnant during the [intervention phase of the](#) trial. Contraceptive measures should be compliant with those described in the Summary of Product Characteristics for the IMPs used in this trial. This should be done as part of the consent process by explaining clearly to the patient the potential dangers of becoming pregnant and also providing each patient with information about highly effective birth control methods which can achieve a failure rate of less than 1% per year when used consistently and correctly. Such methods include:

- combined (estrogen and progestogen containing) hormonal contraception associated with inhibition of ovulation
  - oral
  - intravaginal
  - transdermal
- progestogen-only hormonal contraception associated with inhibition of ovulation
  - oral
  - injectable
  - implantable
- intrauterine device (IUD)
- intrauterine hormone-releasing system ( IUS)
- bilateral tubal occlusion
- vasectomised partner
- sexual abstinence

 Hormonal contraception may be susceptible to interaction with the IMP(s), which may reduce the efficacy of the contraception method. Please refer to the SmPC for each relevant IMP(s).

 Vasectomised partner is a highly effective birth control method provided that partner is the sole sexual partner of the women of child bearing potential trial participant and that the vasectomised partner has received medical assessment of the surgical success.

 sexual abstinence is considered a highly effective method only if defined as refraining from heterosexual intercourse during the entire period of risk associated with the study treatments. The reliability of sexual abstinence needs to be evaluated in relation to the duration of the intervention phase of this clinical trial and the preferred and usual lifestyle of the subject.

Contraceptives should be used from the time the patient joins the trial until completion of the intervention phase of the trial. Please refer to the SmPCs for each IMP for guidance of any continued requirement of contraceptive use when treatment with the IMP(s) is complete. It should be explained to each male patient that if his partner is pregnant or breast-feeding when he enters the trial, the patient should use barrier method contraception (condom plus spermicidal gel) to prevent the unborn baby or the baby being exposed to the IMP(s) (systemic chemotherapy).

The Investigator must ensure that all patients are aware at the start of a clinical trial of the importance of reporting all pregnancies (in themselves and their partners) that occur whilst being treated with the IMP(s). If a trial participant or a trial participant's partner does become pregnant during treatment with the IMP(s) it must be reported to the Chief Investigator (and the Sponsor) within 24 hours of the site staff becoming aware of it using the **PREGNANCY NOTIFICATION FORM**. Participants who become pregnant must be discontinued from trial treatment immediately. It is the Investigator's responsibility to obtain consent for follow-up from the patient or patient's partner. The Sponsor will follow-up all pregnancies for the pregnancy outcome via the Investigator and document on the **PREGNANCY NOTIFICATION FORM**.

The Investigator should offer counselling to the participant and/or the partner, and discuss the risks of continuing with the pregnancy and the possible effects on the foetus. With appropriate consent, monitoring of the participant and/or the partner and the baby should continue until the conclusion of the pregnancy. Pregnancy is not considered an AE unless a negative or consequential outcome is recorded for the mother or child/foetus. If the outcome meets the serious criteria, this would be considered an SAE and reported as such.

## APPENDIX 2: CHEMOTHERAPY

### 1 OVERVIEW AND TIMING OF SYSTEMIC CHEMOTHERAPY

The patient and the medical oncologist may choose one of the chemotherapy regimens described below. Single agent systemic chemotherapy will be permitted if patient comorbidity precludes the use of concomitant oxaliplatin and is typically reserved for frail patients. The planned choice of systemic chemotherapy is a stratification variable for randomization, therefore the treatment decision should be made upfront, when the patient consents to trial registration. The same chemotherapy is offered to the control arm and both of the intervention arm subgroups but the timing will vary, as summarised in the Table 1 below:

**The timing and number of cycles of chemotherapy according to regimen and randomization arm:**

| Systemic Chemotherapy Regimen a                                                                                                                                                                                                                                                              | Control Arm       | Intervention arm                     |                                     |
|---------------------------------------------------------------------------------------------------------------------------------------------------------------------------------------------------------------------------------------------------------------------------------------------------------|-------------------|--------------------------------------|-------------------------------------|
|                                                                                                                                                                                                                                                                                                         |                   | Good Response sub-group b | Poor Response sub-group             |
| CAPOX (3 weekly cycle)                                                                                                                                                                                                                                                                                  | 8 cycles post-op  | 8 cycles during deferral of surgery  | 4 cycles pre-op
4 cycles post-op |
| FOLFOX (2 weekly cycle)                                                                                                                                                                                                                                                                                 | 12 cycles post-op | 12 cycles during deferral of surgery | 6 cycles pre-op
6 cycles post-op |
| Capecitabine                                                                                                                                                                                                                                                                                            | 8 cycles post-op  | 8 cycles during deferral of surgery  | 4 cycles pre-op
4 cycles post-op |
| 5-FU (Fluorouracil)                                                                                                                                                                                                                                                                                     | 12 cycles post-op | 12 cycles during deferral of surgery | 6 cycles pre-op
6 cycles post-op |
| a For details relating to the preparation and administration of these drugs: see manufacturer's product information and refer to local guidelines.
b if the patient declines deferral of surgery post-operative systemic chemotherapy should be given i.e. as for control arm. |                   |                                      |                                     |

- In this trial the above medications will be provided, prepared and administered by the Investigator site as per local guidelines. This appendix includes recommended chemotherapy regimens. Local sites are permitted to follow their standard practice for the dosage, administration and dose adjustment of systemic chemotherapy.
- Dose banding and capping as per local guidelines is permitted for CAPOX, FOLFOX and single agent therapy as long as the delivered dose falls within  $\pm 7\%$  of the calculated dose
- Local sites are permitted to follow their local guidance for the provision of supportive medication (e.g anti-emetics)
- Assessments including but not limited to routine blood tests, pregnancy tests, physical examinations including weight, ECGs, vital signs, CEA, and renal function should be performed as per local practice prior to and during systemic treatment.

## 1.1 CHEMOTHERAPY TREATMENT POST-SURGERY

Adjuvant chemotherapy should commence 4-12 weeks (ideally 6-8 weeks) after surgery. If this is delayed beyond 12 weeks, for example due to post-operative complications, the patient must be discussed with the lead centre (RMH) in order to determine if proceeding with adjuvant treatment is still appropriate.

## 1.2 CHEMOTHERAPY TREATMENT IN INTERVENTION ARM – GOOD RESPONDERS

If regrowth occurs while patient receives chemotherapy, patient should proceed to surgery and the pathology discussed at a MDT meeting to decide whether the remaining cycles of chemotherapy should be given post-operatively. A **SURVEILLANCE Form** should be completed.

## 1.3 CHEMOTHERAPY TREATMENT IN INTERVENTION ARM – POOR RESPONDERS

If patients have had a dose reduction during neoadjuvant (pre-operative) chemotherapy, the same dose as the finishing dose of the neoadjuvant chemotherapy should be started post-operatively.

## 1.4 CHANGES TO REGIMEN CHOICE DURING TREATMENT

It is not recommended to cross over regimens unless there is a compelling clinical reason to do so. However a mid-treatment switch is allowed in this protocol and this should be documented on the CHEMOTHERAPY CRF. NOTE: Be aware if crossing from FOLFOX to CAPOX, capecitabine may cause increased toxicity when given after recent folinic acid and a capecitabine-dose reduction is required.

If a patient switches to a therapy not included in this protocol then please contact the TRIGGER Trial Office to discuss with the Chief Investigator. The change in therapy should be recorded on the CHEMOTHERAPY CRF and a PROTOCOL DEVIATION Form should be completed.

## 2 RECOMMENDED CAPOX REGIMEN (3 WEEKLY CYCLE)

| Drug         | Dose                        | Day(s) in cycle | Administration          |
|--------------|-----------------------------|-----------------|-------------------------|
| Oxaliplatin  | 130 mg/m        | 1               | 2-6 hr i.v. infusion*   |
| Capecitabine | 1700 mg/m  /day | 1-14            | PO in two divided doses |

\* standard infusion to be given over 2hours. For patients who have a hypersensitivity reaction to oxaliplatin, it is recommended that infusion be given over 4hrs. For patients experiencing laryngopharyngeal spasm, it is recommended that infusion be given over 6hrs

Patients will be treated every 3 weeks (1 cycle) for a total of 8 cycles. As described in Table 1 patients randomized to the intervention arm in the poor response subgroup will receive 4 cycles pre-operatively and 4 cycles post-operatively.

Oxaliplatin 130mg/m^2 diluted in 250-500ml 5% dextrose will be given as an IV infusion over 2-6 hours. The maximum BSA for determining the dose of oxaliplatin and capecitabine is 2m^2.

Capecitabine will be administered as oral tablets: Capecitabine 1700mg/m^2/day (850mg/m^2 twice daily) will be administered orally for 14 days followed by 7 days' rest.

**Patients aged 75 or above** will have a reduced starting dose: Capecitabine (1300mg/m^2/day) (650mg/m^2 twice daily) given orally divided into 2 split doses in the morning and evening for 14 days followed by 7 days' rest. Oxaliplatin 100mg/m^2 will be given every 3 weeks (the maximum BSA for determining the dose of oxaliplatin and capecitabine is 2m^2).

### 3 RECOMMENDED CAPECITABINE MONOTHERAPY REGIMEN (3 WEEKLY CYCLE)

Single agent capecitabine can be used if concomitant oxaliplatin is contraindicated.

| Drug         | Dose                                                               | Day(s) in cycle | Administration          |
|--------------|--------------------------------------------------------------------|-----------------|-------------------------|
| Capecitabine | 2000 mg/m  /day
(1000mg/m  twice daily) | 1-14            | PO in two divided doses |

**Patients aged over 75** will have a reduced starting dose: Capecitabine 1500mg/m^2/day (750mg/m^2 twice daily) given orally divided into 2 split doses in the morning and evening for 14 days followed by 7 days' rest.

**Patients aged 80 or above** will have a reduced starting dose: Capecitabine 1000mg/m^2/day (500mg/m^2 twice daily) given orally divided into 2 split doses in the morning and evening for 14 days followed by 7 days' rest.

### 4 RECOMMENDED FOLFOX REGIMEN (2 WEEKLY CYCLE)

| Drug                                                                                                              | Dose                   | Day(s) in cycle | Administration                                   |
|-------------------------------------------------------------------------------------------------------------------|------------------------|-----------------|--------------------------------------------------|
| Oxaliplatin                                                                                                       | 85 mg/m    | 1               | 2-6 hr i.v. infusion                             |
| Folinic acid a                                                                                         | 400 mg/m   | 1               | 2 hr i.v. infusion concurrently with oxaliplatin |
| 5-FU                                                                                                              | 400 mg/m   | 1               | i.v. bolus                                       |
|                                                                                                                   | 2400 mg/m  | 1-2             | 48 hr i.v. infusion b                 |
| a where local practice is to use levofolinic acid, then this is permitted at the locally approved dose |                        |                 |                                                  |
| b or 46 hours if this is local practice.                                                               |                        |                 |                                                  |

Patients will be treated every 2 weeks (1 cycle) for a total of 12 cycles. As described in Table 1 patients randomized to the intervention arm in the poor response subgroup will receive 6 cycles pre-operatively and 6 cycles post-operatively.

## 5 RECOMMENDED 5-FU MONOTHERAPY REGIMEN (2 WEEKLY CYCLE)

5-FU/Folinic acid can be used if concomitant oxaliplatin is contraindicated

| Drug                                                                                                                                                                     | Dose                   | Day(s) in cycle | Administration                                   |
|--------------------------------------------------------------------------------------------------------------------------------------------------------------------------|------------------------|-----------------|--------------------------------------------------|
| Folinic acid a                                                                                                                                                | 400 mg/m   | 1               | 2 hr i.v. infusion concurrently with oxaliplatin |
| 5-FU                                                                                                                                                                     | 400 mg/m   | 1               | i.v. bolus                                       |
|                                                                                                                                                                          | 2400 mg/m  | 1-2             | 48 hr i.v. infusion b                 |
| a where local practice is to use levofolinic acid, then this is permitted at the locally approved dose
b or 46 hours if this is local practice. |                        |                 |                                                  |

## 6 TOXICITY AND DOSE MODIFICATIONS

### 6.1 TOXICITY AND DOSE MODIFICATION NOTES

- Toxicity will be graded using CTCAE version 4.0.
- In general, the **maximum allowable toxicity related treatment delay is 3 weeks**. Any patient whose treatment is delayed for longer than 3 weeks due to treatment related toxicity should discontinue that phase of therapy. If it is clinically appropriate to do so, patients should proceed with the next phase of treatment within the study. However, due to the complex nature of the study treatment, it is not possible to pre-specify management for every situation. Therefore, if a scenario not addressed in this section arises, then the chief investigator should be contacted to discuss further management within the study.
- **For patients in the intervention arm poor response subgroup due to undergo surgery:** Where possible, and as long as it is still clinically appropriate to do so, patients should proceed to surgery, even if they are unable to complete pre-operative treatment due to toxicity when they have recovered adequately.
- If an unacceptable treatment delay due to toxicity from combination chemotherapy or oxaliplatin occurs, it would be acceptable for treatment to be completed with fluoropyrimidine alone, provided the treatment delaying toxicity is not considered to be due to the fluoropyrimidine itself. It is not permissible for patients to receive oxaliplatin without a fluoropyrimidine analog.
- If treatment is stopped due to patient choice or toxicity, subsequent treatment will be at the discretion of the treating clinician. This should be documented on the **CHEMOTHERAPY Form**. A **DISCONTINUATION OF TRIAL TREATMENT Form** should also be completed. All patients who withdraw from treatment should remain on follow-up within the trial.

Only toxicities deemed treatment-related by the investigator will require dose modifications. The recommended dose modifications of the study medications in the event of commonly known toxicities are outlined below. Clinical discretion should be used in the event of any serious toxicity not listed below and any other dose modifications may be performed at the discretion of the investigator. All concerns or uncertainties should be discussed with the Chief Investigator.

### 6.2 DOSE MODIFICATIONS

- Dose modification guidance is given for reference. Local sites are permitted to use their local standard dose modification protocols.

### 6.3 CAPOX/CAPECITABINE MONOTHERAPY

#### 6.3.1 HAEMATOLOGICAL TOXICITY:

Grade 3 infection/fever associated with neutropenia (ANC<1) at any time on treatment requires a subsequent 25% dose reduction in oxaliplatin

Grade 4 infection/fever associated with neutropenia (ANC<1) at any time on treatment requires a subsequent 50% dose reduction in oxaliplatin

Asymptomatic neutropenia and thrombocytopenia on the day of treatment would require the following dose reductions for the CAPOX regimen:

| Neutrophil count
( $\times 10^9/l$ ) | CTCAE grade | Action                                                                                                                                          |
|-----------------------------------------|-------------|-------------------------------------------------------------------------------------------------------------------------------------------------|
| $\geq 1.0$                              | 0-2         | Full dose of all drugs                                                                                                                          |
| 0.5-0.9                                 | 3           | Stop capecitabine and delay oxaliplatin until recovery (e.g. 1 week later). Restart capecitabine at full dose. Reduce oxaliplatin by 25%        |
| $< 0.5$                                 | 4           | Stop capecitabine and delay oxaliplatin until recovery (e.g. 1 week later). Restart capecitabine at 75% of the dose. Reduce oxaliplatin by 50%. |
| Platelet count
( $\times 10^9/l$ )   | CTCAE grade | Action                                                                                                                                          |
| $\geq 75$                               | 0-1         | Full dose of all drugs                                                                                                                          |
| 50-74                                   | 2           | Stop capecitabine and delay oxaliplatin until recovery (e.g. 1 week later). Restart both capecitabine and oxaliplatin at full dose.             |
| 25-49                                   | 3           | Stop capecitabine and delay oxaliplatin until recovery (e.g. 1 week later). Restart capecitabine at 75% of the dose. Reduce oxaliplatin by 25%  |
| $< 25$                                  | 4           | Stop capecitabine and delay oxaliplatin until recovery (e.g. 1 week later). Restart capecitabine at 75% of the dose. Reduce oxaliplatin by 50%  |

### 6.3.2 NON-HAEMATOLOGICAL TOXICITIES:

#### 6.3.2.1 CAPECITABINE NON-HAEMATOLOGICAL TOXICITY:

Refer to table below for dose modifications for diarrhoea, nausea, vomiting, stomatitis

| CTC Grade | 1 st Appearance Dose | 2 nd Appearance Dose | 3 rd Appearance Dose | 4 th Appearance Dose |
|-----------|---------------------------------|---------------------------------|---------------------------------|---------------------------------|
| 0-1       | 100%                            | 100%                            | 100%                            | 100%                            |
| 2         | delay* then 100%                | delay* then 75%                 | delay* then 50%                 | discontinue                     |
| 3         | delay* then 75%                 | delay* then 50%                 | discontinue                     | discontinue                     |
| 4         | discontinue or delay* then 50%  | discontinue                     | discontinue                     | discontinue                     |

\*interrupt treatment until resolved to Grade 0-1

All patients should be prescribed symptomatic treatment such as loperamide, sucralfate and emollients for diarrhoea, stomatitis and hand-foot syndrome respectively according to local practice.

**Renal function:** for creatinine clearance 30-50mls/min the dose of capecitabine should be reduced by 25%. If the dose has already been reduced by 25% for age, then an additional dose reduction for renal function is not required.

**Liver function:** capecitabine can cause an increase in bilirubin and liver transaminases. This is usually mild and of no clinical significance. However, if the bilirubin increases to >3x normal or AST/ALT increases to >2.5x normal the capecitabine should be withheld until the bilirubin <2.5 x ULN and ALT < 2.5 x ULN, at which point treatment can recommence without dose reduction.

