| 
 
In all cases treatment should be delayed until recovery of toxicity to grade 2 (except thrombocytopenia, where recovery should be to grade 1 (≥75x10^9/L)). Omission of the bolus of 5-FU can be considered in cases of neutropenia and thrombocytopenia.
 
If a patient develops grade 4 neutropenia, delay chemotherapy until recovery to grade 2 (Neutrophils ≥1.0x10^9/l) and proceed with chemotherapy without any dose reductions for subsequent cycles with GCSF support on days 7-11 post chemotherapy.
 
 |                                                                                              |                                                |                                  |                               |

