**Permitted, non-permitted medications and medications to be used with caution**

- Investigators should refer to the SmPC for each of the drugs used for details relating to contraindications, special warnings and precautions for use, and interactions with other medical products and other forms of interactions. Up to date versions of these are available at <http://emc.medicines.org.uk/>
- Live vaccines** (including inhaled flu vaccines) should not be administered to immunocompromised patients, including those receiving chemotherapy or within 6 months after receiving chemotherapy.

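### Capecitabine liver rule: a raised AST can start the hold, but the restart condition names only bilirubin and ALT, so no AST recovery limit is set

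*Protocol*

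**What the plan says.** The liver-function paragraph of Appendix 2, section 6.3.2.1, has a hold condition and a release condition in one sentence.

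- Hold: "if the bilirubin increases to >3x normal or AST/ALT increases to >2.5x normal".
- Release: "capecitabine should be withheld until the bilirubin <2.5 x ULN and ALT < 2.5 x ULN". Once this is met, treatment may restart with no dose reduction.

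Four other parts of Appendix 2 bear on how the rule is used:

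- Section 1 leaves testing during treatment to the site: "routine blood tests, pregnancy tests, physical examinations including weight, ECGs, vital signs, CEA, and renal function should be performed as per local practice". It also gives sites freedom over dosing: "Local sites are permitted to follow their standard practice for the dosage, administration and dose adjustment of systemic chemotherapy".
- Section 6.1 sets a general maximum of 3 weeks for a toxicity-related delay, after which that phase of therapy should stop. It refers situations that the section does not address to the chief investigator, and adds: "All concerns or uncertainties should be discussed with the Chief Investigator".
- Section 6.2 presents the dose modifications as reference guidance: "Local sites are permitted to use their local standard dose modification protocols".
- Section 7 points to the product information: "Investigators should refer to the SmPC for each of the drugs used for details relating to contraindications, special warnings and precautions for use".

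**The concern.** A hold rule should end on the same measurements that started it. Here AST can start the hold but has no part in ending it. What follows depends on what the site measures, which the protocol leaves to local practice.

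If both enzymes are measured, an AST-triggered hold can be released, read literally, while AST is still above the level that triggered it. If AST/ALT is taken to mean whichever enzyme the site measures, an AST-only site can start the hold but has no ALT value with which to end it.

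What is at stake is the clarity of a safety instruction for patients on CAPOX or single-agent capecitabine. No trial estimate, error rate or between-arm comparison is at issue.

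**Working it through.** The protocol states no numerical result to reproduce here, so the check is one of logic, followed by a search for a limit elsewhere.

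**Inputs (Appendix 2, section 6.3.2.1).** All values are multiples of ULN. The trigger is worded relative to normal and the release relative to ULN; I take the two as the same.

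- Hold = bilirubin > 3, or AST > 2.5, or ALT > 2.5.
- Release as written = bilirubin < 2.5 and ALT < 2.5.
- Release as corrected = bilirubin < 2.5 and each measured transaminase < 2.5.

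**Cases.** Bilirubin is 1 throughout. The enzyme values are illustrative, chosen to exercise the logic, and are not frequencies. The rows with an enzyme at 2 show the state after recovery from a hold already in force.

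| Site measures | Values | Hold trigger met? | Release as written | Release as corrected |
|---|---|---|---|---|
| ALT only | ALT 4 | yes | not met | not met |
| ALT only, recovered | ALT 2 | no longer | met | met |
| AST only | AST 4 | yes | cannot be evaluated | not met |
| AST only, recovered | AST 2 | no longer | cannot be evaluated | met |
| Both | AST 4, ALT 2 | yes | met | not met |
| Both, recovered | AST 2, ALT 2 | no longer | met | met |

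The written rule behaves properly only in the ALT-only rows, where AST plays no part. In the AST-only rows the release stays undefined even after AST has fallen. With AST 4 and ALT 2, hold and release are satisfied together, because 4 > 2.5 triggers the hold while 1 < 2.5 and 2 < 2.5 release it.

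**Is an AST limit given elsewhere for capecitabine?**

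- The footnote in section 6.3.2.1 that requires resolution to Grade 0-1 belongs to the table for diarrhoea, nausea, vomiting and stomatitis. It does not cover liver enzymes.
- Section 6.3.2.2 deals with oxaliplatin and covers stomatitis, diarrhoea and neurosensory toxicity.
- The note "In all cases treatment should be delayed until recovery of toxicity to grade 2" is in section 6.4, which governs FOLFOX and 5-FU monotherapy.
- The 3-week maximum in section 6.1 limits how long a hold may last. It does not say what AST value ends it.

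None of these supplies the missing limit.

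**The case against.** The strongest reply is that nobody would follow the literal reading. If hold and release are both satisfied at AST 4 and ALT 2, an AST-triggered hold never operates at all, and a clinician would not read the sentence that way. While AST remains above the trigger, the reason for withholding is still visible on the page, and the restart is permitted, not required. An AST-only site is hypothetical, since the protocol names none. Such a site would also have the 3-week maximum and the chief investigator to fall back on. The dose rules are optional guidance, and investigators are sent to the SmPC, which may cover the point. The same paragraph describes these enzyme rises as usually mild and of no clinical significance.

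Most of this stands as a limit on consequence. Sensible clinicians will often wait for AST to fall, and the provisions cited reduce the chance of harm. The SmPC is not available here, so whether it closes the practical gap cannot be judged.

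It does not make the sentence correct. None of the provisions cited in the protocol states an AST recovery value. Referral to the chief investigator helps only if the site notices the gap, and a site measuring both enzymes would simply see a release condition that has been met. For an AST-only site, the 3-week maximum runs with no written criterion for ending the hold before it expires. If ALT in the release was shorthand for both enzymes, the correction only writes down the intent. If AST was left out on purpose, the protocol should say so, because it was put into the trigger.

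**Conclusion.** The rule is wrong as written: its stop and restart conditions do not match, and the protocol gives no AST recovery limit for capecitabine. Confidence in the wording mismatch is high. No claim is made about how often it would affect a patient.

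Severity is minor. The reach is confined to CAPOX and capecitabine patients at sites that apply this appendix instead of a local protocol. The number affected cannot be given, because the protocol does not state how often AST rises without ALT, which enzymes each site measures, or how many sites use the appendix. A restart with raised AST is what the literal wording permits, not what most clinicians would be expected to do. Dose reductions made earlier for other reasons stand. The primary endpoint is unaffected, and no bias between arms is claimed.

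The conclusion assumes that normal in the trigger means ULN. It also assumes that AST/ALT lets AST start the hold, either alongside ALT or as the only enzyme measured; the same correction serves both readings.

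**What to change.** Reword the release in the liver-function paragraph of Appendix 2, section 6.3.2.1, so that capecitabine is withheld until bilirubin is below 2.5 x ULN and each of AST and ALT that is measured is below 2.5 x ULN. The clinical leads should confirm that these are the intended limits.

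This changes one clause and can go into the next protocol amendment. It needs no additional tests, visits or data.
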